### The plan and methods of follow-up

Every patient will be followed for at least 1 year if the aneurysm is not ruptured or treated by surgery. The Estimated Primary Completion Date is December 30, 2021. Thus, the follow-up procedure is expected to last until December 30, 2022. The participants will be contacted by phone or Internet at 3 months and 12 months and contacted face to face at 6 months. Images of computed tomography angiography (CTA)/magnetic resonance angiography (MRA)/digital subtraction angiography (DSA) and vascular ultrasound will be obtained at 6 months. The participants’ visit and evaluation schedule is shown in Table 1.

**Table 1 Tab1:** Participants’ visit and evaluation schedule

Visit number	Screening period	Follow-up period		
	1	2	3	4
Research arrangement	Screening	90 ± 14 days	180 ± 30 days	365 ± 30 days
Informed consent	√			
Selection criteria	√			
Baseline information	√			
History of disease and history of medicine taking	√			
Medicine taking		√	√	√
Symptoms and physical examination	√	√	√	√
Electrocardiogram	√			
Routine blood test	√			
Blood sugar	√			
Blood lipid	√			
Homocysteine	√			
Head CT/MRI	√	√	√	√
CTA/MRA/DSA	√		√	
Vascular ultrasound	√		√	
mRS score	√	√	√	√
HAMA score	√	√	√	√
End point evaluation		√	√	√
Adverse event evaluation		√	√	√

Participants should visit at least once a year after 1 year

*CT* computed tomography, *MRI* magnetic resonance imaging, *CTA* CT angiography, *MRA* magnetic resonance angiography, *DSA* digital subtraction angiography, *mRS score* modified Rankin scale score, *HAMA score* Hamilton anxiety score

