### Measures to reduce bias

*Control of selection bias* This is a nationwide population-based study. Twenty centers selected from different regions of China are involved in this study. The status of diagnosis and treatment in different regions of China will be investigated in this study and will be involved in the final analysis. In addition, the patients in each center will be screened consecutively according to the selection criteria.

*Control of information bias* Blinding is being adopted in this study. The clinical research associates (CRAs) will be blinded to the study design. The statistical analysis will also be conducted blindly.

A standardized training program will be created and implemented to ensure that all of the work is undertaken by well-trained CRAs and CRCs.

The double-check process will be implemented in the process of data collection. The quality of the data will be evaluated again before analysis. Unqualified data will be corrected if possible or will be removed if the information about its accuracy is not available. The impact of missing information will be fully considered and will be subject to special analysis.

Regularly communicating with the patients will help improve the quality of the follow-up. The CRAs will call the patients on a regular basis. Furthermore, mobile applications, such as Wechat (an instant messaging and social media application), will be used to establish effective communication channels. In the case of a nonresponding patient, the CRA will try to contact the patient again several days later.

*Control of confounding factors* As many potential confounding factors as possible will be identified. Considering that this is an observational study, overly strict selection criteria are not used.

The design and implementation of this study are guided by statistical experts. Statistical methods such as standardized rate, stratified analysis, multivariate logistic regression analysis and propensity score matching will be adopted to identify the influential variables. These influential variables will be taken into consideration when calculating the annual rupture rate and when establishing the multifactor analysis model in CIAP-2.

Subgroup analyses and a case–control study design will be used when calculating the rupture rate in specific populations. The selection criteria for the exposure group and the control group will be set reasonably, and multiple groups of controls will be used if necessary.

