### Statistical analysis

Statistical description of the clinical data.Continuous variables are expressed as the mean ± standard deviation and compared by one-way analysis of variance. Categorical variables are expressed as the quantity (rate) and compared with the Chi-square test. Continuous variables that do not conform to a normal distribution are expressed using the median and interquartile range and are compared by the Mann–Whitney nonparametric test. P < 0.05 is considered significant.Annual rupture rate calculation.The overall annual rupture rate of UIAs is the proportion of aneurysms that ruptured in one year, which will be calculated with the data from the 1-year assessment. When analyzing the rate in a specific population, a subgroup analysis will be performed.Assessment of influential factors.Multivariate regression analysis will be used to calculate the OR of high-risk factors for the development and rupture of aneurysms. The 95% confidence interval will also be calculated. The receiver operating characteristic curve (ROC) will be used to determine the cutoff value with the best sensitivity and specificity for the prediction of rupture.

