An observational design was chosen for this study, in which the diagnosis and treatment of disease will not be affected. Compared with an interventional study, more patients with different characteristics can be enrolled in a real-world study that has lower internal validity but superior external validity. The results of the real-world study better represent the current status of the diagnosis and treatment of diseases. At the same time, the study can be implemented for a long period of time, include a large sample size, and provide benefits for less of an investment. Furthermore, the conclusions drawn from the study might be more easily extrapolated to and more useful in clinical practice. Lastly, registration studies are safer for the participants [15, 16]. Despite the shortcomings [17], a real-world study is still the most suitable design for this study.

The UIA research platform will be established in this study based on multicenter cooperation and will take advantage of the EDC system. There are 3 cohorts in this platform: the Cohort of Unruptured Aneurysm without Treatment (CIAP-1, CIAP-2, CIAP-3), Cohort of Unruptured Aneurysm with Treatment (CIAP-4), and Cohort of Ruptured Aneurysm (CIAP-5). The relationships among these five studies have been clearly described in the protocol of CIAP-2 and CIAP-4 [12, 13]. The patients in this study (CIAP-1) will be transferred to the cohort in CIAP-5 if the IA ruptures. They will be transferred to the cohort in CIAP-4 if the IA is surgically treated. Under these conditions, observation will be discontinued for this study. The patients in CIAP-1 will also be enrolled in CIAP-2/CIAP-3 if they meet the additional selection criteria (Figs. 1, 2).

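### Logistic odds ratios for rupture ignore time at risk cut short by treatment, so they are biased for any factor associated with treatment

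*Protocol article*

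**What the plan says.** Three parts of the Protocol article bear on this.

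- **Effect measure and model.** Statistical analysis: "Multivariate regression analysis will be used to calculate the OR of high-risk factors"; both aneurysm development and rupture are covered. Measures to reduce bias, under control of confounding: "multivariate logistic regression analysis and propensity score matching will be adopted to identify the influential variables".
- **Follow-up.** The section on follow-up states: "Every patient will be followed for at least 1 year if the aneurysm is not ruptured or treated by surgery". The Discussion adds that a surgically treated patient moves to CIAP-4 and a patient with a rupture moves to CIAP-5, and that then "observation will be discontinued for this study". The note under Table 1 asks for at least yearly visits after the first year.
- **Treatment.** The Discussion says that the observational design leaves diagnosis and treatment unaffected. It also reports serious over-treatment of unruptured aneurysms in China, which might affect the conclusions about the rupture rate. No percentage is given.

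The rupture rate is likewise a one-year proportion: it "is the proportion of aneurysms that ruptured in one year, which will be calculated with the data from the 1-year assessment". Nowhere does the article mention person-time, censoring, or a Cox or Poisson model, and it gives no rule for treated patients in the odds-ratio analysis.

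**The concern.** Logistic regression on rupture yes/no treats every patient as if observed for the same length of time. Here time at risk depends on when, and whether, the aneurysm is treated, and clinicians make that choice in usual care. If a feature makes treatment more likely or earlier, patients with that feature have less time in which a rupture can be seen. The odds ratio then mixes the feature's effect on rupture with its effect on treatment.

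Identifying possible risk factors for rupture is one of the two main purposes given in the Background, and the results are meant to guide the prediction model in CIAP-2. A factor that is weakened or exaggerated here is passed on in that form.

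**Working it through.** The article gives no power, event count or treated fraction for the risk-factor analysis, so there is no figure of the plan to reproduce. The check asks what the stated model returns when the true effect is known.

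**Inputs**

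- From the article: logistic odds ratio; observation ends at treatment; expected annual rupture rate 1% (Sample size calculation).
- Assumed: rupture hazards h of 0.03 per year (feature present) and 0.01 per year (feature absent), so the true hazard ratio is 3. In each group a fraction f is treated at time m (years).

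**Formulas, over one year**

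- Observed rupture risk: r = (1−f)(1−e^(−h)) + f(1−e^(−hm))
- Untreated and unruptured at one year: s = (1−f)e^(−h)
- Treated patients kept as non-ruptured: OR = [r₁/(1−r₁)] / [r₀/(1−r₀)]
- Treated, unruptured patients excluded: OR = (r₁/s₁) / (r₀/s₀)
- Person-time: T = r/h, so the rate ratio is (r₁/T₁)/(r₀/T₀) = h₁/h₀

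**No treatment.** The risks are 0.02955 and 0.00995, and the OR is 3.03. At this event rate the odds ratio itself is a good approximation to the hazard ratio.

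**One pattern in full: f = 0.6, m = 0.15 against f = 0.2, m = 0.25**

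- r₁ = 0.4 × 0.02955 + 0.6 × 0.00449 = 0.01452
- r₀ = 0.8 × 0.00995 + 0.2 × 0.00250 = 0.00846
- Kept: (0.01452/0.98548) / (0.00846/0.99154) = 1.73
- s₁ = 0.4 × 0.97045 = 0.38818; s₀ = 0.8 × 0.99005 = 0.79204
- Excluded: (0.01452/0.38818) / (0.00846/0.79204) = 3.50

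**All patterns, true hazard ratio 3**

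| Feature present (f, m) | Feature absent (f, m) | OR, kept | OR, excluded | Rate ratio |
|---|---|---|---|---|
| 0.6, 0.15 | 0.2, 0.25 | 1.73 | 3.50 | 3.00 |
| 0.5, 0.20 | 0.2, 0.20 | 2.15 | 3.47 | 3.00 |
| 0.4, 0.20 | 0.1, 0.20 | 2.22 | 3.36 | 3.00 |
| 0.3, 0.20 | 0.3, 0.20 | 3.02 | 3.03 | 3.00 |

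The last row has equal treatment in both groups, and there the bias all but disappears.

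**A second timing model.** This takes a 0.7% yearly rupture risk without the feature and treatment at a constant hazard within the year, with 5% to 30% treated without the feature against 20% to 70% with it (all assumed). For a true ratio of 3 the OR is 2.08 to 2.77 (kept) or 3.30 to 4.88 (excluded). For a true ratio of 2 it is 1.38 to 1.84 or 2.19 to 3.24. If all treatment instead falls at month 1, with 30% against 70% treated, a true ratio of 2 becomes 0.99 (kept) or 2.32 (excluded). The rate ratio equals the true value throughout.

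**The case against.** The strongest reply is that the size rests entirely on assumed treatment rates. This stands. The article does not say how many patients are treated, when, or for which features, and the row with 60% treated at about eight weeks is the most extreme in the table. Nor does it adopt the coding that causes the larger shrinkage. With treated patients excluded, the table's odds ratios are only about 11% to 16% above 3.03 (3.36/3.03 and 3.50/3.03). So neither the size nor the direction of the error in this study is known. What remains is that both available codings are biased once treatment depends on the factor, so a coding rule in a fuller analysis plan would not repair the stated model.

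One might also point to the safeguards in the section on bias. Stratification and propensity score matching deal with confounding, and the promised special analysis concerns missing information. None of these accounts for unequal time at risk.

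A reader might infer more than the text supports:

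- *That size, location and daughter sac are the factors distorted.* They are the cited predictors and plausible drivers of treatment, but the article does not say what triggers treatment. The Discussion also names drug and disease history, genetics, lifestyle and stress as open questions. Any of these unrelated to treatment would be nearly unaffected.
- *That the ROC cut-off is chosen and assessed on the same data.* The article says only that the curve will determine the cut-off. Validation is commonly left to the full plan.
- *That too many factors will be fitted to about 45 ruptures.* The sentence "As many potential confounding factors as possible will be identified" concerns identifying confounders, not putting them all in one model. The count (4696 × 0.95 × 1% ≈ 45) ignores treatment exits and ruptures after one year.

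**Conclusion.** The point holds as a mismatch between the stated model and the design. The article fixes a logistic odds ratio for rupture, while its follow-up rules make time at risk depend on treatment. For a factor that raises both rupture risk and treatment, the bias is toward the null, or as far as it, when treated patients are kept, and away from the null when they are excluded. If the factor lowers the chance of treatment, the directions reverse. If it is unrelated to treatment, the odds ratio is close to correct.

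Confidence is high for the mechanism and low for the size. Odds ratios of 1.7 to 2.2 or 3.4 to 3.5 for a true hazard ratio of 3 illustrate what the assumed treatment patterns would do; they do not predict this cohort. The exact agreement of the rate ratio with the true value also assumes that, within each group, treatment is unrelated to rupture risk.

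**What to change.** In Statistical analysis and in the paragraph on control of confounding, replace the logistic odds ratio for rupture with a cause-specific Cox hazard ratio or a Poisson rate ratio. End time at risk at rupture, treatment, death or last contact, and cluster the variance by patient where several aneurysms per patient are analysed.

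Adjust for recorded features likely to drive treatment, such as size, location and morphology. State that censoring at treatment is assumed independent of rupture risk given those covariates, and that residual confounding by indication may remain. The change removes the time-at-risk error but not that confounding.

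The cost is revised wording and modest programming, with no added visits or patients. The model needs dates of rupture, treatment, death and last contact. Transfer to CIAP-4 or CIAP-5 should leave a date, but the sponsor should confirm that the follow-up case report form records all four.

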### Study design and methods

The China Intracranial Aneurysm Project (CIAP) is a prospective, observational registry study of the natural courses, risk factors for the onset and rupture, treatment methods, comorbidity management and other aspects of IAs. To the best of the authors’ knowledge, the CIAP, sponsored by Chinese Science and Technology Ministry and National Stroke Prevention Project Committee, is the largest ongoing project evaluating IAs in China; it currently includes 5 studies. The first study in the CIAP was designed to set up and manage a UIA database of 5000 individuals and calculate the annual rate of rupture of those aneurysms. The second study aimed to identify the risk factors for aneurysm rupture and develop a multidimensional predictive model for rupture. The third study was designed to explore the strategy of antithrombotic therapy in UIA patients complicated by ischemic cardiovascular/cerebrovascular diseases. The fourth study was designed to compare the therapeutic effects of intervention surgery and craniotomy surgery in the treatment of UIAs. The fifth study was designed to develop a standardized clinical pathway for early-stage cerebral hemorrhage caused by aneurysms [12, 13].

CIAP-1, intended to establish an open research platform and a nationwide UIA cohort, is the first and most fundamental task of the entire project. It is designed to achieve the following aims:Establish a nationwide public health and research platform administered by researchers, doctors, clinical center managers, Contract Research Organizations (CROs) and health management companies.Establish a nationwide prospective UIA cohort as a joint effort from 20 clinical centers.Clarify the natural history and annual rupture rate of UIAs in China.Identify the characteristics of people with intracranial aneurysms and look for possible causes of IAs.Screen for risk factors for UIA rupture and provide guidance to CIAP-2, which is designed to establish a multidimensional model to predict UIA rupture.

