### Recruitment of participants

Patients will be enrolled consecutively in all of the clinical centers and through China’s Stroke Prevention Project Committee. Patients with UIAs will be enrolled when they first visit the clinical center or are registered by the Stroke Prevention Project Committee. Patients with multiple aneurysms will also be enrolled when at least one aneurysm remains untreated. The patients will be selected according to the following selection criteria.

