#### Inclusion criteria

Diagnosis of untreated unruptured intracranial aneurysms (by CTA, MRA or DSA).Modified Rankin Scale (mRS) score of 3 or less.Age older than 18 years.Provision of consenting to participate in the study.

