### Outcomes

The primary outcome: the rupture of the aneurysm.The secondary outcome: obvious changes in the morphology of the aneurysm (maximum diameter increase ≥ 1 mm or new daughter sac forms); or a new serious clinical symptom develops (such as headache).

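### Odds ratios for aneurysm onset, and possible causes of aneurysms, cannot come from a cohort in which everyone has an aneurysm at entry

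*Protocol article*

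**What the plan says.** Under Statistical analysis, the third item (influential factors) states that multivariate regression will be used to "calculate the OR of high-risk factors for the development and rupture of aneurysms", with 95% confidence intervals. Among the five CIAP-1 aims under Study design and methods is: "Identify the characteristics of people with intracranial aneurysms and look for possible causes of IAs".

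The first inclusion criterion is "Diagnosis of untreated unruptured intracranial aneurysms (by CTA, MRA or DSA"). Recruitment follows the same rule by both of its routes: "Patients with UIAs will be enrolled when they first visit the clinical center or are registered by the Stroke Prevention Project Committee".

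Under Outcomes, the article lists "The primary outcome: the rupture of the aneurysm" and, as secondary, "obvious changes in the morphology of the aneurysm (maximum diameter increase ≥ 1 mm or new daughter sac forms") or a new serious clinical symptom. The formation of a new aneurysm is not listed.

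Controls appear under Measures to reduce bias, where "a case–control study design will be used when calculating the rupture rate in specific populations". The Discussion describes the wider platform: "There are 3 cohorts in this platform: the Cohort of Unruptured Aneurysm without Treatment (CIAP-1, CIAP-2, CIAP-3"), followed by a treated cohort (CIAP-4) and a ruptured cohort (CIAP-5).

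**The concern.** An odds ratio for developing an aneurysm compares exposure in people who have one with exposure in people who do not. The article promises such a measure, or at least uses wording that most readers will take that way, while describing recruitment that supplies only the first group. The sister cohorts do not fill the gap, because their members also have aneurysms.

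What is at stake is the interpretation of later results. If exposure frequencies among patients, or contrasts between one kind of patient and another, are reported under an aim that speaks of causes, they may be read as evidence on why aneurysms form. The design cannot support that reading, and the study is meant to inform prevention policy.

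**Working it through.** **Inputs.** Planned size: 4696 over four years (Sample size calculation). Expected annual rupture rate: 1% (same section). Aneurysm status at entry: present in everyone (Inclusion criteria, Recruitment of participants).

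**The plan's own figure.** No sample size is given for an analysis of development. The stated 1173 per year and 4696 over four years are for the precision of the rupture rate. From the stated inputs, n = 1.96² × 0.01 × 0.99 / 0.006² = 1056.4. Dividing by 0.95 for the stated 5% drop-out gives 1112.0. Dividing by 0.90 gives 1173.8, and 4 × 1174 = 4696, so the printed figures match a 10% allowance. That mismatch is a separate matter. Nothing below depends on it, and 4696 is used only as the stated size.

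**Odds ratio for having an aneurysm.** Let a and b be exposed and unexposed people with an aneurysm, and c and d exposed and unexposed people without one.

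- a + b = 4696
- c + d = 0, so c = 0 and d = 0
- OR = (a × d) / (b × c) = 0 / 0, which is undefined
- The variance of log OR, 1/a + 1/b + 1/c + 1/d, is infinite

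The same holds in a multivariate model: when the outcome takes one value for every participant, no coefficient for any exposure can be estimated. Replacing 4696 with the 5000 named elsewhere in the article changes a + b only.

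**Odds ratio for rupture, for contrast.** 1% of 4696 is about 47 ruptures in one year, against 4696 − 47 = 4649 without rupture (before losses and surgical treatment). Both outcome groups exist, so this odds ratio is estimable in principle.

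**What development means.** The article does not define it.

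- For onset: the Abstract and the opening of Study design and methods describe the project's scope by pairing onset with rupture, just as the regression sentence pairs development with rupture. The Discussion uses development when it says that what brings aneurysms about is still unknown. Where the article means growth, under Outcomes, it speaks of changes in morphology.
- For growth: growth is a listed secondary outcome, and formation is not.

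Onset is the better reading, but growth is not excluded.

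**Possible sources of non-cases in the article.** The controls under Measures to reduce bias are tied to rupture rates in specific populations. The platform's three cohorts are untreated, treated and ruptured aneurysms. Registration through the Stroke Prevention Project Committee is described for patients with unruptured aneurysms. None provides an aneurysm-free person.

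**The case against.** The strongest reply is that development may mean progression. Read against the Outcomes section, the regression would then concern growth or a new daughter sac together with rupture, and both sets of odds ratios could be estimated. This stands in part. A reader might infer that half of the planned regression is certainly lost, and the documents do not support that, because the term is undefined. But this reading does not help the aim: causes of intracranial aneurysms cannot be taken to mean growth of one already present. And if growth was meant, the sentence still needs to name the outcome.

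A second reply is that a whole aim is not lost. That is correct. A reader might infer that one of the five aims cannot be answered, but its first half, describing people with aneurysms, is feasible in this cohort. The second half is also worded as exploration and does not itself promise an odds ratio.

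A third reply is that new aneurysms might be seen on the six-month vascular imaging, so some formation could be studied. A reader might therefore count it as something the cohort already measures. The Outcomes section does not list it. If it were added, participants without a new aneurysm would be the non-cases, and the result would concern further formation in people who already have an aneurysm, not the causes of a first one.

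A last reply is that an article leaves detail to the full protocol. That would answer a complaint about missing detail. Here the article states both an analysis and an enrolment rule, and on the onset reading the two do not fit. An analysis plan cannot supply people who were not enrolled.

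**Conclusion.** The point holds in limited form. From the cohort described, an odds ratio for aneurysm onset cannot be estimated: there are 0 non-cases at any sample size. This rests only on the enrolment criteria and on the absence of an aneurysm-free group anywhere in the article. That the regression sentence means onset is probable, not certain. If it means growth, the fault is an undefined term not linked to the secondary outcome. The clause on causes in the aims is unsupported on either reading.

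The extent is one term in one analysis sentence and half of one aim. A reader might infer that the main results are in doubt, but the documents do not support that: the stated main purposes, the primary outcome, the sample size, the annual rate and the ROC analysis all concern rupture and are unaffected by this point.

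**What to change.** In the regression sentence under Statistical analysis, replace development and rupture with two named outcomes: rupture, and the morphological change already listed under Outcomes (a gain of 1 mm or more in maximum diameter, or a new daughter sac).

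In the aims under Study design and methods, keep the characteristics of people with intracranial aneurysms as an explicitly descriptive aim and delete the clause on possible causes.

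Add new aneurysms on follow-up imaging only if they are defined as an outcome, with a statement that the result applies to people who already have an aneurysm.

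The cost is the rewording of one sentence and half an aim, and a narrower stated claim. If the sponsor wishes to keep onset as a question, the alternative is to describe an aneurysm-free comparison group and its source. That would be a change of design and far more costly.

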**Methods:**

The China Intracranial Aneurysm Project (CIAP) is a prospective, observational, multicenter registry study of the natural courses, risk factors for the onset and rupture, treatment methods, comorbidity management and other aspects of intracranial aneurysms. To date, there are five studies in the CIAP. CIAP-1 is a prospective observational cohort study of UIAs. More than 5000 patients who will be followed for at least 1 year are expected to be enrolled in this cohort. These participants come from more than 20 centers that represent different regions in China. Enrollment began on May 1, 2017, and will take approximately 5 years. A nationwide online database of UIAs will be built. Participants’ basic, lifestyle, clinical and follow-up information will be collected. The blood samples will be stored in the Central Biological Specimen Bank. Strict standards have been established and will be followed in this study to ensure efficient implementation.

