### Statistical methods

#### Sample size calculation

The sample size is calculated based on the following formula:$$ n = \frac{{u_{\alpha }^{2} p\left( {1 - p} \right)}}{{d^{2} }} $$

The annual rupture rate is expected to be 1% [9], the allowable error is d = 0.6%, the tests will be two-sided, with an α level of 0.05. It is calculated that 1173 subjects need to be enrolled in 1 year, and 4696 subjects are needed in 4 years. The expected drop-out rate is 5%. Drop-out is identified as enrolled patients who cannot be included in the primary analysis because, for example, they did not complete the follow-up in time or they lack key information.

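### The rupture cut-off is picked for best sensitivity and specificity on about 45 expected ruptures, so sensitivity read at that cut-off in the same patients will be too high unless it is corrected

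*Protocol article*

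**What the plan says.** Under Statistical analysis, in the item on influential factors, the protocol article plans a multivariate regression to give odds ratios with 95% confidence intervals. It then plans a ROC curve to "determine the cutoff value with the best sensitivity and specificity for the prediction of rupture". It does not say whether the curve is drawn for a single factor or for a fitted score, and it describes no correction for having chosen the cut-off on the data.

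The Sample size calculation gives the figures that set the number of events: "The annual rupture rate is expected to be 1% [9], the allowable error is d = 0.6" per cent, "It is calculated that 1173 subjects need to be enrolled in 1 year, and 4696 subjects are needed in 4 years", and "The expected drop-out rate is 5" per cent. The size was set for the precision of a rate, not for a prediction rule.

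On CIAP-2, the aims under Study design and methods include "Screen for risk factors for UIA rupture and provide guidance to CIAP-2", and the same section describes CIAP-2 as developing a predictive model. The Discussion places CIAP-1, CIAP-2 and CIAP-3 in one untreated cohort and adds: "The patients in CIAP-1 will also be enrolled in CIAP-2/CIAP-3 if they meet the additional selection criteria".

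**The concern.** Choosing the cut-off with the best sensitivity and specificity means taking the maximum over many candidate thresholds. Part of that maximum is chance, and the chance part does not recur in new patients. The fewer the events, the larger it is. Non-events number in the thousands, so specificity is well determined and nearly all of the error falls on sensitivity, which is the share of ruptures that the cut-off catches. If the cut-off belongs to a regression model fitted to the same patients, overfitting of the coefficients adds to the error.

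The article says (Discussion) that its conclusions should give evidence to guide the management of unruptured aneurysms. A reported sensitivity that is 10 or 20 points too high would make a threshold look safer than it is.

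**Working it through.** **Step 1. The plan's own sample size.** Inputs from Sample size calculation: p = 0.01, d = 0.006, two-sided α = 0.05 (u = 1.96).

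- n = 1.96² × 0.01 × 0.99 / 0.006² = 1056.4.
- With the stated 5% drop-out: 1056.4 / 0.95 = 1112 per year, and 4 × 1112 = 4448.
- With 10% drop-out: 1056.4 / 0.90 = 1173.8 per year, and 4 × 1174 = 4696.

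The printed 1173 and 4696 therefore match a 10% allowance and not the stated 5%. That is a separate discrepancy. It matters here only through the event count.

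**Step 2. Expected ruptures at 1 year.**

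- 4696 × 0.95 × 0.01 = 44.6, about 45.
- 4696 × 0.90 × 0.01 = 42.3 if the loss is 10%.
- 5000 × 0.95 × 0.01 = 47.5, using the Abstract's enrolment figure; 5000 × 0.01 = 50 with no loss.
- Over the 0.79–1.15% interval quoted in the Discussion: 4696 × 0.95 × 0.0079 = 35.2 and 4696 × 0.95 × 0.0115 = 51.3.

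**Step 3. Cut-off on a single marker.** Simulated normal scores with 45 events and 4461 − 45 = 4416 non-events. The cut-off maximises sensitivity + specificity. "Same patients" is the value read in the data that chose it; "new patients" is its true value. The true area is assumed.

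| True area | Sensitivity, same patients | Sensitivity, new patients | Excess (points) |
|---|---|---|---|
| 0.6 | 63.0% | 55.3% | 7.7 |
| 0.7 | 69.1% | 62.3% | 6.8 |
| 0.8 | 76.1% | 70.2% | 5.9 |

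With 500 events instead of 45, the excess falls to between 1 and 2 points, so the small event count is the cause.

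**Step 4. Cut-off on a fitted logistic model.** The number and strength of the predictors are assumed. Weak setting: four real predictors, odds ratio 1.35 per SD each, the rest noise. Stronger settings: five real predictors that together give a true area of 0.7 or 0.8, the rest noise.

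| Predictors | Weak: same / new (excess) | True area 0.7: same / new (excess) | True area 0.8: same / new (excess) |
|---|---|---|---|
| 5 | 69% / 57% (12) | 70% / 59% (11) | 77% / 68% (8) |
| 10 | 68% / 51% (17) | 72% / 56% (16) | 78% / 66% (11) |
| 20 | 72% / 47% (25) | 73% / 51% (22) | 79% / 61% (18) |

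Excesses are taken before rounding. Repeat runs differ by about a point. Specificity agrees between same and new patients to within about 0.2 points in every cell. In the weak 20-predictor case the area is 0.74 in the same patients against 0.61 in new ones.

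**Step 5. Precision.** Even with no optimism, 32 of 45 ruptures caught (71%) has an exact 95% interval of 56% to 84%. Sensitivity should not be reported as a bare figure.

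**Step 6. Does CIAP-2 supply the check?** Study design and methods gives it model development, guided by CIAP-1. The Discussion puts it in the same untreated cohort and has eligible CIAP-1 patients enter it. On this text it offers no sample known to be separate from the one that chose the cut-off.

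**The case against.** The strongest reply is that this is a condensed article. One sentence says how the cut-off is determined and nothing says how its accuracy will be reported; bootstrap or cross-validation may be set out in a fuller document. That stands, and the absence of a validation paragraph is not the point here. What remains is a stated rule, a maximised cut-off, combined with an event count that the article's own figures make small.

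Several stronger readings are tempting and should not be drawn:

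- *That accuracy will be reported uncorrected from the same patients.* The article does not say so. The bias arises if it is.
- *That factors are prescreened at P < 0.05 and only the survivors passed to CIAP-2.* The significance threshold closes the item on descriptive comparisons; no such selection step or hand-over is stated. If a prescreen of 20 candidates were used, the gap would shrink but remain: 67% against 50% at odds ratio 1.35, and 74% against 63% at 1.65.
- *That 72% against 47% is the expected error.* It is the far end, for an assumed 20-predictor model with weak effects. A single-marker cut-off is an equally open reading and gives 6 to 8 points.
- *That CIAP-2 enrols the same patients and is offered as validation.* Entry depends on additional criteria, the article does not say whether others also enter, and it never calls CIAP-2 a validation of this cut-off. The detailed relationships are left to separate protocols that are not shown.
- *That this cut-off will decide treatment.* Only the study's conclusions in general are said to guide management.

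The count of 45 is also not fixed. The 1-year assessment is tied to the annual rate, not expressly to the ROC analysis, so later yearly visits could add events. Leaving observation at surgery, with over-treatment acknowledged in the Discussion, could remove some.

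**Conclusion.** The concern holds in a limited form. With a cut-off chosen for best sensitivity and specificity on about 45 expected ruptures (35 to 51 over the quoted interval), sensitivity read in the same patients is biased upward. The direction is certain. The size depends on assumptions that the article does not settle:

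- about 6 to 8 points for one marker with a true area of 0.6 to 0.8;
- about 12 to 25 points for a fitted model with 5 to 20 predictors when effects are weak, and 8 to 22 points when the predictors together reach a true area of 0.7 to 0.8.

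Specificity is little affected. CIAP-2 as described does not by itself provide an independent check. This is a matter of reporting a secondary analysis properly. It does not touch the annual rupture rate and is not a contradiction in the protocol. The change should be made.

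**What to change.** In Statistical analysis, in the item on influential factors, add to the ROC sentence:

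- State whether the cut-off applies to a single factor or to a fitted score.
- Repeat every data-driven step (any variable selection, the model fit and the choice of cut-off) within each bootstrap sample, and subtract the average optimism.
- Report the optimism-corrected area, sensitivity and specificity with confidence intervals and the number of ruptures behind them.
- Label the cut-off exploratory until it has been tested in patients outside CIAP-1. If CIAP-2 is to serve that purpose, restrict the test to its patients who were not in CIAP-1.

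The bootstrap step needs no new data or visits. The cost is a little more analysis work and less favourable reported accuracy. Testing outside CIAP-1 needs other patients, but only before the exploratory label is dropped.
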